## Abstract

**Background:**

For treating deep caries lesions, selective or stepwise (one- and two-step) incomplete excavation seems advantageous compared with complete caries removal. However, current evidence regarding the success, as defined by not requiring any retreatments, or survival of teeth after different excavations is insufficient for definitive recommendation, especially when treating deciduous teeth. Moreover, restoration integrity has not been comparatively analyzed longitudinally, and neither patients’, dentists’ or parents’ preferences nor the clinical long-term costs emanating from both initial and retreatments have been reported yet.

**Methods/Design:**

The planned study is a prospective multicenter, two-arm parallel group, randomized controlled clinical trial comparing selective and stepwise excavation in deciduous molars with deep, active caries lesions without pulpal symptoms. We will recruit 300 children aged between three and nine-years-old with a minimum of one such molar. Patients participating in another study, or those with systemic diseases, disabilities or known allergies to used materials as well patients with teeth expected to exfoliate within the next 18 months will be excluded. After inclusion, sequence generation will be performed. Initial treatment will follow dental routine. During excavation, leathery, moist and reasonably soft dentin will be left in proximity to the pulp followed by adhesive restoration of the cavity. Afterwards, patients’, dentists’ and parents’ subjective assessment of the treatment will be recorded using visual analogue or Likert scales. Re-examination will be performed after six months, and only then teeth will be allocated to one of the two interventions. Selectively excavated teeth will not be treated further, whilst for stepwise caries removal, a second excavation will be performed until only hard dentin remains. Clinical re-evaluations will be performed after 12, 24 and 36 months. Restorations will be reassessed using modified Ryge criteria. Objectively or subjectively required retreatments will determine success and survival. Retreatments will be evaluated both subjectively and regarding generated costs.

**Discussion:**

Based on the results of the trial, decision-making for treating deep caries lesions in deciduous molars based on multiple criteria should be feasible.

**Trial registration:**

Clinicaltrials.gov identifier: NCT02232828 (registered on 29 November 2014).

## Background

The treatment of deep caries lesions is associated with significant risks for the pulp, including pulpal exposure and postoperative pulpal complications, which might eventually compromise the retention of the tooth [1]. Moreover, treating deep lesions might be associated with pain and subjective burden both during and after treatment, and might generate long-term costs due to retreatments being required [2,3].

For deciduous teeth, various treatments for deep lesions have been described: complete excavation aims at removing all infected and affected carious dentin, with the inherent risk of pulpal exposure. In contrast, stepwise (two-step) excavation leaves carious dentin after the initial excavation step, then seals residual caries under a temporary restoration, and re-enters the cavity in a second step to eventually attempt complete excavation. This approach is thought to facilitate arrest and remineralization of the lesion and to induce development of tertiary dentin, thereby reducing the risk of pulpal exposure and postoperative complications after the second excavation step [4,5]. Since several studies found sealed residual lesions to be clinically and microbiologically arrested, the need to re-enter was increasingly questioned within the last decade [6]. Selective (one-step) incomplete or partial excavation seals carious dentin under a definitive restoration, omitting any re-entry [7]. Sealing the lesion is thought to deprive residual bacteria from dietary carbohydrates and has been found to exert significant antibacterial effects, thus arresting the lesion [8,9].

However, doubts remain regarding the effects of sealed carious dentin on the long-term quality of the restoration [10]. Moreover, it remains unknown if patients prefer one treatment over the other, which might be especially relevant when treating children. Several studies comparing complete with selective or stepwise excavation of deciduous teeth have been published, but only one three-arm study compared selective with stepwise excavation of primary teeth (Table 1). In addition, none of these studies assessed patient- or dentist-centered outcomes, that is, preferences, or analyzed clinically assessed long-term costs emanating from both excavations.

**Table 1 Tab1:** **Published randomized controlled trials comparing different excavations of dentin caries in deciduous molars**

**Study**	**Study type; setting; country**	**Participants (age); teeth; lesion**	**Intervention (number of teeth)**	**Control (number of teeth)**	**Follow-up, drop-out**	**Pulp exposure (PE)**
						**Pulp symptoms (PS)**
						**Failure (F)**
						**Caries progression (CP)**
Leksell *et al.* 1996 [11]	Multicenter parallel-group RCT; university and clinics; Sweden	116 (6-16); 134 primary molars; caries with ‘risk of pulp exposure’	Stepwise (64) (‘remaining innermost layer of carious dentin’ left); re-entry after 8-24 weeks	CR (70) (‘hard’)	24 weeks, 4.3% yearly	PE: 18% stepwise, 40% CR
						PS: Non-exposed teeth remained asymptomatic
						F: 0% stepwise, 0% CR
Foley *et al*. 2004 [12]	Split-mouth RCT; university; Scotland	44 (3-9); 120 primary molars; dentin caries	Selective (36) restored with BCC and GIC; one-step (43) restored with just GIC	CR (41)	24 months, 11% yearly	PS: More abscesses in BCC group
						F: 23% GIC, 33% BCC, 22% CR
						CP: Caries increase highest in CR
Ribeiro *et al*. 1999 [13]	Parallel-group RCT; university; Brazil	38 (7-11); 48 primary molars; dentin caries without risk of pulp exposure	Selective (24) (‘partially removed, soft and moist dentine left’)	CR (24) (dye)	12 months, 0% yearly	PS: 0% selective, 4% CR
						F: 0% selective, 4% CR
						CP: 25% selective
Orhan *et al*. 2010 [14]	Parallel-group RCT; university; Turkey	123 (4-15); 154 (94 deciduous and 60 permanent) molars; caries >3/4 dentin	Stepwise (50) (‘thin layer of soft tissue left’); Stepwise (49); re-entry after 3 months	CR (55)	12 months, 0% yearly	PE: 6% selective, 8% stepwise, 22% CR
						PS: 0% selective, 2% stepwise, 5% CR
						F: 0% selective, 2% stepwise, 5% CR
Magnusson and Sundell, 1977 [15]	Parallel-group quasi-RCT; university; Sweden	62 (5-10); 110 primary molars; caries ‘considered for stepwise excavation’	Stepwise (55) (‘soft layer of dentin over the pulp’); re-entry after 4-6 weeks	CR (55) (‘until hard’)	No follow-up	PE: 11% stepwise, 53% CR
						PS: 5% stepwise, CR not followed-up
Heinrich *et al*. 1991 [16]	Parallel-group RCT; university; Germany	125 (6-7); 125 primary molars; deep caries	Stepwise (52) (‘slightly soft’); re-entry after 6-8 weeks	CR (52) (‘hard with explorer’)	16 months, 12% yearly	PE: 15% stepwise, 31% CR
						PS: 6% stepwise, 13% CR
						F: 6% stepwise, 13% CR
Lula *et al*. 2009 [17]	Parallel-group RCT; university; Brazil	30 (5-8); 36 primary molars; caries >1/2 dentin	Selective (18) (‘only superficial necrotic dentin removed from the pulpal and axial walls’)	CR (18) (dye)	6 months, 5.7% yearly	PE: 0% selective, 22% CR
						PS: 0% selective, 7% CR
						F: 0% selective, 14% CR
Phonghanyudh *et al*. 2012 [18]	Bi-centered parallel-group RCT; dental hospitals; Thailand	276 (6-11); 276 primary molars; caries ≥1/3	Selective (92) (‘soft carious tissues at EDJ completely removed, without further removal of carious dentin’)	CR (92)	12 months, 2.5% yearly	PE: 0% selective, 2% CR
						PS: 1% selective, 2% CR
						F: 18% selective, 14% CR restoration failure
						CP: No caries progression in any group
Franzon *et al*. 2014 [19]	Split-mouth RCT; university; Brazil	51 (3-8); 124 primary molars; Caries in ‘inner quarter of dentin’	Selective (61) (‘leathery’)	CR (67)	24 months, 2.0% yearly	PE: 2% selective, 28% CR
						PS: 10% selective, 0% CR

BCC: black copper cement, CR: complete caries removal, EDJ: enamel-dentinal junction, GIC: glass ionomer cement, RCT: randomized controlled trial.

### Objectives and hypotheses

The study aims at comparing the success (the probability of not requiring any re-interventions) and the survival (the probability of not requiring tooth removal) of selectively excavated versus stepwise excavated vital, non-symptomatic deciduous molars with deep lesions. In addition, we assess the restoration integrity of selectively excavated versus stepwise excavated deciduous molars, evaluate the preference of patients, parents and dentists for one of both strategies, and comparatively assess the costs associated with each strategy.

Our primary hypothesis is that success rates differ significantly between selectively excavated and stepwise excavated teeth. Secondary hypotheses are that restoration integrity is assumed to significantly differ between selectively excavated and stepwise excavated teeth. Moreover, we hypothesize that patients’, parents’ and dentists’ preference is significantly different for selectively excavated versus stepwise excavated teeth. Eventually, both initial and long-term costs of excavation methods are supposed to significantly differ.

## Methods/Design

### Overview

The planned study is a secondary care-based prospective, multicenter, two-arm parallel-group, randomized controlled trial at three pediatric university dental clinics in Germany: the Charité - Universitätsmedizin Berlin, the Ernst-Moritz-Arndt University Greifswald and the RWTH University of Aachen. We plan to enroll 300 patients with one or more deeply carious, sensitive and non-symptomatic deciduous molar. One molar per patient will be randomly allocated to receive one of two treatments (selective or stepwise excavation). The total follow-up time will be three years after completion of the initial treatment. Success, survival and restoration integrity will be assessed after one, two and three years. Patients’, parents’ and dentists’ preference will be assessed after each treatment using visual analogue or Likert rating scales. Costs will be assessed for the initial and follow-up treatments and will be based on a micro-costing approach. The study has been approved by the ethics committee of the Charité - Universitätsmedizin Berlin (approval number: EA4/057/14), the Ernst-Moritz-Arndt University Greifswald (approval number: BB 112/14) and the RWTH University of Aachen (approval number: EK 283/14). The study is registered at Clinicaltrials.gov (identifier: NCT02232828).

### Setting and participants

The study will take place in three dental university clinics in Eastern, Northern and Western Germany. All are publically funded teaching hospitals. We will include children aged between three and nine-years-old with a minimum of one sensitive, clinically and radiographically non-symptomatic, retainable, deeply carious deciduous molar with a caries lesion involving either only the occlusal or the occlusal and exactly one proximal (mesial or distal) surface. The lesion will be required to radiographically extend into the inner third of the dentin (D3) and show signs of activity, such as plaque retention, papillary bleeding and/or softness of the surface [20]. Patients will require parental consent for participation. In addition, patients’ cooperation for treatment under no or only local anesthesia will be expected.

Patients participating in another study, patients with parents planning to move away within the next three years, patients who are not residents of the federal states of Berlin, Brandenburg, Mecklenburg-Vorpommern and Nordrhein-Westfalen, as well as patients with systemic diseases or disabilities will not be included. Patients with known allergies to dental materials used within the study as well as those with teeth expected to exfoliate within the next 18 months will also not be included.

### Sample size

The required sample size was calculated based on the primary outcome parameter, success (see below). We anticipate a hazard ratio of 1.3 [21] of stepwise excavated compared with selectively excavated teeth. If α = 0.05 and 1-β = 0.9, a sample size of n = 66 per group is required. Assuming an annual drop-out rate of 20%, 114 patients per group will be required. The total required sample size would thus be n = 228. To allow possible subgroup analyses, a total of 300 patients will be recruited (n = 100 per center).

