### Data analysis and statistical evaluation

The statistical evaluation will be performed using SPSS 20.0. Descriptive statistics will be calculated according to distribution of data. Log rank tests will be used to compare success and survival between groups, with effects of possible confounders (age, gender, dental anxiety, cooperation, use of local anesthetics, caries risk, dental arch, first or second molar, surfaces and center) being assessed. Moreover, we will use two-sided independent t tests or Mann-Whitney U test (to compare visual analogue scale results and costs) as well as chi-square tests (to compare restorative integrity and subjective grading of treatments).

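### The stated 66 per group cannot give 90% power at a hazard ratio of 1.3: the log-rank test needs about 611 events, and the 300 children can supply at most 300

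*Protocol article*

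**What the plan says.** The Sample size section of the protocol article ties the calculation to the primary outcome, success, meaning that no re-intervention is needed. The effect is given as a hazard ratio: "We anticipate a hazard ratio of 1.3 [21] of stepwise excavated compared with selectively excavated teeth". The next sentence gives the result: "If α = 0.05 and 1-β = 0.9, a sample size of n = 66 per group is required". Drop-out is then added: "Assuming an annual drop-out rate of 20%, 114 patients per group will be required", and "The total required sample size would thus be n = 228". The recruitment target is set above that: "To allow possible subgroup analyses, a total of 300 patients will be recruited (n = 100 per center".

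The analysis is a survival comparison. Under Data analysis and statistical evaluation: "Log rank tests will be used to compare success and survival between groups". The Overview says that one molar per child is randomised and that follow-up lasts three years after the initial treatment is completed. The Sample size section gives no event count, baseline failure rate, sidedness or formula.

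**The concern.** Power of a log-rank test depends on the number of events, and a hazard ratio of 1.3 is a small effect that needs several hundred of them. A total of 132 teeth looks far too small for it at any failure rate. This paragraph is the only justification for the size of the trial on its primary outcome. If it is wrong, the trial is presented as having 90% power for an effect that it would more likely miss than find under moderate failure rates. The subgroup rationale fails with it, because it treats 228 as enough for the main comparison and the other 72 children as spare.

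**Working it through.** **Inputs**
- Hazard ratio 1.3, alpha 0.05, power 0.90, 66 per group, 20% annual drop-out, 114 per group, 228 in total, 300 recruited: Sample size.
- Log-rank test: Data analysis and statistical evaluation.
- One randomised molar per child, so at most one primary event per child: Overview.
- Equal allocation: implied by the equal group sizes.
- Two-sided test: assumed, because the hypothesis has no direction ("Our primary hypothesis is that success rates differ significantly between selectively excavated and stepwise excavated teeth"). One-sided results are also given.

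**1. The plan's own figures.** The drop-out step can be reproduced: 66 × 1.2³ = 114.05, and 2 × 114 = 228. The base figure of 66 could not be reproduced by any standard survival calculation from a hazard ratio of 1.3.

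**2. Events required.** Schoenfeld: D = 4(z₁₋α/₂ + z₁₋β)² / (ln HR)².
- (1.95996 + 1.28155)² = 10.507 and (ln 1.3)² = 0.06884, so D = 610.6, rounded up to 611.
- Freedman: 10.507 × (2.3/0.3)² = 617.6, rounded up to 618.
- One-sided alpha 0.05: 498 (Schoenfeld) or 504 (Freedman).
- With power lowered to 80%: 457 two-sided or 360 one-sided (Schoenfeld).

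Every one of these exceeds 300.

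**3. Best case, with every tooth failing.** Two-sided power = Φ(√(D/4) × ln 1.3 − 1.960). Hazard ratio detectable with 90% power = exp(2 × 3.2415/√D).

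| Teeth = events | Power at HR 1.3 | HR for 90% power |
|---|---|---|
| 132 (66 per group) | Φ(1.507 − 1.960) = 33% | 1.76 |
| 228 (114 per group) | Φ(1.981 − 1.960) = 51% | 1.54 |
| 300 (recruited) | Φ(2.272 − 1.960) = 62% | 1.45 |

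One-sided, 132 events give 44.5% power and 300 give 73.5%.

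**4. Comparison of proportions at a fixed time.** If the two success proportions are linked by a hazard ratio of 1.3 (p₂ = p₁^1.3), the smallest sample over all baseline rates is 476 per group two-sided (388 one-sided). This does not give 66 either.

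**5. Illustration only.** The section gives no failure rate, so these rates are assumptions: 300 children, exponential failure at h and 1.3h, 20% annual loss treated as censoring, and three years at risk.

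| Assumed annual failure | Expected events | Power at HR 1.3 |
|---|---|---|
| 5% | about 36 | about 12% |
| 10% | about 68 | about 19% |
| 20% | about 122 | about 30% |

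With 2.5 years at risk after allocation at six months, events fall to about 32, 61 and 112, and power is slightly lower.

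**6. A route to 66.** If 1.3 is read as a ratio of success proportions, for example 0.713 against 0.927, the two-sided two-proportion formula without continuity correction gives [1.95996√(2 × 0.82 × 0.18) + 1.28155√(0.713 × 0.287 + 0.927 × 0.073)]² / 0.214² ≈ 65.6, that is 66 per group. This is a different effect measure, and neither rate is stated in the section.

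**The case against.** The strongest defence is that the number may be right for a calculation that was mislabelled. The protocol article defines success as a probability and hypothesises that success rates differ, and step 6 shows that a ratio of proportions of 1.3 can lead to 66. The cited source for the 1.3 is not available to settle this. The possibility stands, and it is why the fix first asks what was calculated. It does not make the paragraph correct, which says hazard ratio and leads to a log-rank test.

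A second defence is that an article may leave the formula and the failure rate to the full protocol. That is fair for what is missing, but here the effect size, alpha, power and sample size are all printed, and no unseen failure rate reconciles them.

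A third is that the scenarios in step 5 depend on choices. This is correct. The failure rates are assumed, the time at risk could be 2.5 years, and the Missing data text counts drop-outs as non-success while Table 3 censors them. Step 5 therefore does not carry the point. Counting drop-outs as failures cannot lift events above 300 either.

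Three further inferences are tempting but unsupported:
- **That 66 cannot be an event count because no failure rate is given.** An event count needs only the hazard ratio, alpha, power and allocation. A failure rate is needed only to turn events into patients.
- **That a non-significant result will be taken as equivalence.** The protocol article states only a difference hypothesis and proposes no equivalence or non-inferiority claim.
- **That 300 was fixed by feasibility.** The only reasons given are possible subgroup analyses and 100 children per centre.

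**Conclusion.** The point holds as an internal contradiction in the Sample size section. A hazard ratio of 1.3 at 90% power needs 611 events two-sided, against ceilings of 132, 228 and 300. The conclusion rests on equal allocation and at most one primary event per child. It does not depend on the failure rate, on sidedness, on Schoenfeld or Freedman, or on how drop-outs are handled. Best-case two-sided power is 33%, 51% and 62%; actual power will be lower to the extent that teeth do not fail. Whether the sample size was miscalculated or the effect measure mislabelled cannot be decided from the document, and either way the paragraph is wrong as written. It must be corrected, because it states a power for the primary outcome that the design does not have.

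**What to change.** In the Sample size section:
- Withdraw the statement that 66 per group (228 after drop-out) gives 90% power at a hazard ratio of 1.3.
- State the effect measure, formula, sidedness and baseline failure rate actually used. If 1.3 was a ratio of success proportions, correct the label and give both rates.
- State the number of events expected from the 300 children, with the time at risk and drop-out handling assumed, and either the power at a hazard ratio of 1.3 or the hazard ratio detectable with 90% power.
- Remove the implication that 300 exceeds what the main comparison needs and so leaves room for subgroup analyses. Label subgroup analyses exploratory.

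Under Data analysis and statistical evaluation, add that the hazard ratio will be reported with its 95% confidence interval alongside the log-rank test.

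The cost is wording only. No extra patients are needed to make the correction; the downside is a much less favourable stated power.

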### Allocation and blinding

If more than one primary molar is eligible, the decision as to which tooth will be included into the study will be performed using random number tables (WH) before treatment is commenced. Sequence generation will be performed after inclusion via random number tables (WH). Allocation will be performed via sealed opaque envelopes after the six-monthly recall examination (six months after selective excavation) by the treating dentists. Thus, both the first excavation step and the first re-examination will be performed blinded as to whether further excavation will be performed or not. Clinical follow-up examinations will also be performed blinded to treatment group allocation. Blinding during the second excavation step and blinding of patients as to which treatment was performed will not be possible, but patients will be informed not to reveal treatment allocation to the examiner during follow-up examinations.

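### The drop-out allowance adds 20% a year where it should divide by 80% retention: 66 per group becomes 129, not 114, and the stated total of 228 should be 258

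*Protocol article*

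**What the plan says.** The Sample size section of the protocol article bases the calculation on the primary outcome, success, and gives a base number: "If α = 0.05 and 1-β = 0.9, a sample size of n = 66 per group is required". It then allows for losses: "Assuming an annual drop-out rate of 20%, 114 patients per group will be required". Doubling gives the overall requirement: "The total required sample size would thus be n = 228". Recruitment is set at 300, 100 at each of the three centers, and the only reason given for going beyond 228 is that subgroup analyses may be wanted.

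The period over which losses accrue comes from the Overview: "The total follow-up time will be three years after completion of the initial treatment". The abstract places re-evaluations at 12, 24 and 36 months. The Missing data section confirms that the sample size was meant to cover loss to follow-up. The inflation formula is not printed.

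**The concern.** An allowance for drop-out should return the base number once the assumed losses have occurred. Adding 20% a year does not offset losing 20% a year: each year multiplies the number by 1.2 × 0.8 = 0.96, so a gap opens and widens with time. The figure of 114 looks like the result of adding.

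What is at stake is the trial's stated minimum. Anyone who treats 228 as the number needed for the primary comparison, for instance if recruitment is slow, would stop below what the plan's own assumptions require. The gap between 228 and 300 is also presented as room for subgroup analyses, and part of it is needed for the main comparison.

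**Working it through.** **Inputs**

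- Base number: 66 per group (Sample size).
- Drop-out: 20% a year (Sample size).
- Follow-up: three years (Overview).
- Stated result: 114 per group, 228 in total (Sample size).
- Planned recruitment: 300, that is 150 per group if groups are equal (Sample size).

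**Reproducing the stated figure**

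66 × 1.2³ = 66 × 1.728 = 114.05, which matches 114. Rounding year by year gives 79, 95 and 114, the same result.

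The usual division forms do not give 114:

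| Form | Result | Rounded up |
|---|---|---|
| 66/0.8 (one year's loss) | 82.5 | 83 |
| 66/0.8² (two years) | 103.1 | 104 |
| 66/0.8³ (three years) | 128.9 | 129 |
| 66/exp(−0.6) (rate of 0.2 a year) | 120.3 | 121 |
| 66/0.4 (60% lost in all) | 165 | 165 |

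**The figure that the assumptions require**

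Retention at three years is 0.8³ = 0.512, so the expected loss is 48.8%.

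- Required per group: 66/0.512 = 128.9, so 129. Check: 129 × 0.512 = 66.0.
- Required in total: 2 × 129 = 258.

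**What 114 delivers**

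- Remaining per group: 114 × 0.512 = 58.4.
- Shortfall against 66: 66 − 58.4 = 7.6 children, or 7.6/66 = about 12%.
- Implied retention if 114 were right: 66/114 = 0.579, a three-year loss of 42.1%. The cube root of 0.579 is 0.833, a loss of 16.7% a year and not 20%.

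**Effect on the planned trial**

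- Remaining per group at the planned size: 150 × 0.512 = 76.8, above 66.
- Surplus over the stated requirement: 300 − 228 = 72.
- Surplus over the corrected requirement: 300 − 258 = 42. The difference is 30 children.

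**Sensitivity to the loss period**

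| Years of loss counted | Required per group | Left from 114 |
|---|---|---|
| 2.5 | 115.3, so 116 | 65.3 |
| 3 | 128.9, so 129 | 58.4 |
| 3.5 | 144.1, so 145 | 52.2 |

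None of the three gives 114.

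**The case against.** Four points can be made for the plan.

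1. **The trial will recruit 300.** This stands. The figure of 58 describes a trial of 228 children, which nobody plans to run. At 150 per group the plan's own 66 is met with about 11 to spare, and no recruitment target changes.

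2. **Lost children are not worthless to the analysis.** The primary comparison is a log-rank test. Table 3 censors children lost to follow-up, so they contribute time until they leave. The Missing data section instead counts drop-outs as failures, which keeps them in the analysed number. Under neither rule do they vanish. As an illustration, assume a low, constant event hazard and losses spread evenly at 20% a year. Mean follow-up is then (1 − 0.512)/(3 × 0.2231) = 72.9% of three years, and the person-time of 66 complete children needs about 66/0.729 = 91 recruited, fewer than 114. So the 12% is a deficit of completers, not a loss of power. But the plan chose a head-count inflation and claims no person-time argument, so this does not make 114 the right result of the step it describes.

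3. **Losses might count only from allocation.** The article says: "Allocation will be performed via sealed opaque envelopes after the six-monthly recall examination (six months after selective excavation) by the treating dentists". With 2.5 years from there to month 36, 114 leaves 65.3, within one child of 66. The article states no such basis, it would give 116 and not 114, and children lost in the first six months would still have to be replaced.

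4. **The formula is inferred.** This is true, although the match is exact. The mismatch between 114 and the stated assumptions does not depend on which formula was used.

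**Conclusion.** The concern holds. On the plan's own inputs (66 per group, 20% lost each year, three years) the requirement is 129 per group and 258 in total. The stated 114 and 228 are 15 and 30 children too low. At 114 per group, 58.4 would be expected to complete, about 12% below 66.

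The practical weight is moderate. Recruitment of 300 covers 258, so this step alone does not leave the trial short. What changes is the stated minimum, and the reserve for subgroups, which falls from 72 to 42. The result assumes that losses compound annually over three years and that the inflation is meant to secure 66 completers per group.

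The base number is a different matter. The plan writes: "We anticipate a hazard ratio of 1.3 [21] of stepwise excavated compared with selectively excavated teeth". By Schoenfeld's formula, that effect needs about 611 events at 90% power with a two-sided 5% test, so 66 per group does not follow from it. Correcting the drop-out step does not repair that, and repeating the step on a corrected base would again leave about 12% too few completers.

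**What to change.** In the Sample size section, replace 114 per group and 228 in total with 129 per group and 258 in total, and print the formula, 66/0.8³. If the base number is revised, apply the same division by 0.512 to the new base in place of printing 129. State that 48.8% of children are expected to be lost by 36 months and that losses are counted over three years. Describe the surplus available for subgroup analyses as 42 children, not the 72 that the present figures imply.

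The cost is a text edit to two figures and a sentence of explanation. This correction by itself needs no further children, since 300 exceeds 258. A revised base number would have to be checked against 300 separately.
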